## Abstract

**Background:**

The mental health impacts of the COVID-19 pandemic have been profound. This paper outlines the study protocol for a trial that tests the efficacy of a brief group-based psychological intervention (*Coping with COVID;* CWC*)*, relative to Supportive Counselling, to reduce distress associated with COVID-19 in a young adult population in Bangalore, India.

**Methods:**

A single-blind, parallel, randomized controlled trial will be carried out via video conferencing in a small group format. Following informed consent, adults that screen positive for levels of psychological distress (Kessler 10 (K-10 score ≥ 20) and have access to a videoconferencing platform will be randomised to an adapted version of CWC (*n* = 90) or Supportive Counselling (SC) (*n* = 90). The primary outcome will be reduction in psychological distress including anxiety and depression at 2-months post treatment. Secondary outcomes include worry, positive wellbeing, and stress in relation to COVID-19.

**Discussion:**

This treatment trial will assess whether CWC will result in reduced distress relative to Supportive Counselling in a young adult population in Bangalore, India. This study will yield important insights into the role of nonspecific factors versus the intervention’s components in impacting COVID-19 related distress.

**Trial registration:**

This trial was prospectively registered on the Australian New Zealand Clinical Trials Registry (ACTRN12621001064897).

**Ethics and dissemination:**

Ethics approval has been obtained from the participating institution, CHRIST University in Bangalore. Results of the trial will be submitted for publication in peer reviewed journals and findings presented at scientific conferences and to key service providers and policy makers.

**Supplementary Information:**

The online version contains supplementary material available at 10.1186/s12888-022-04471-4.

## Background

A global burden of disease study in 2020 estimated that common mental health problems such as major depression and anxiety increased by at least one quarter during the COVID-19 pandemic [1]. This is not surprising given that the early impositions of social and economic restrictions to curtail the spread of infection around the globe came with vast mental health ramifications. Reports of widespread mental distress including stress, anxiety, depression and hopelessness during the early stages of the pandemic intersected with the uncertainties of such strict containment strategies in addition to the fear of infection itself [2–4]. The mental health impacts have been particularly strongly felt in places with low human mobility and high daily infection rates of COVID-19 [5]. Specifically, low- and middle-income countries (LMICs) posed a particular vulnerability to the long-term mental health sequelae of COVID-19. For example, in India the series of strict lockdowns during the early stages of the pandemic came with the sudden closure of commercial activities and educational institutions across the country. The immediate impact of these restrictions was seen in reduced access to essential services, food insecurities and unstable employment [6, 7]. As the impacts of the pandemic have continued, the mental health costs have persisted in LMICs, including India [8]. To this end, several calls have been made to implement evidence-based interventions in a scalable and readily accessible format, under real-world circumstances, to ward off the potential long-term threats of the pandemic, further widening the gap between availability and demands for quality mental health care [9].

Tertiary students were evidenced to be especially susceptive to the adverse effects of quarantine during the COVID-19 pandemic [10], whereby the prolonged closure of educational institutions took a toll on the wellbeing of young adults [11]. Mental health care that would have been otherwise provided by counsellors based within the universities were likely disrupted as a result of the prolonged pandemic closures. These are pertinent forewarnings given that more than three quarters of the world’s population of young people live in LMICs, where the pandemic continues to have ongoing impacts on economic stress, social isolation and loneliness; all known risk factors for the long-term negative impacts of mental health [2]. Indeed, recent evidence during the COVID-19 pandemic has highlighted the potential oversight of the mental health impacts in young people (aged < 24 years) [9]. Importantly, education settings in low-income settings have a pivotal role in shaping social support networks, protecting vulnerable individual from insecure housing, and in the provision of future opportunities for skilled employment. Naturally, the rise in unintended adverse impacts including depression, anxiety, and worry in young adults [12] is an agenda worth addressing within the broader global mental health strategy.

Scalable solutions to mental health care in response to adversity and crises have been a particular focus in recent years. Problem Management Plus (PM+) is one such intervention developed by the World Health Organization (WHO) [13]. As a low-intensity program, PM + was designed to address common mental health problems arising from adversity in LMICs. The intervention comprises of evidence-based techniques including stress management, problem solving, behavioral activation, and social support enhancement [14]. Developed to be delivered by lay personnel involving those without specialist mental health qualifications, PM + has been shown to reduce mental distress and increase wellbeing in those exposed to adversity and crises across diverse demographic groups [15–19]. Recently, an adapted version of this program was delivered via video teleconferencing, *Coping with COVID* (CWC) was found to reduce worry, anhedonia, and contamination fears arising during the pandemic [20]. In this study, the group-based program addressed the transdiagnostic nature of mental health problems reported during the COVID-19 pandemic and was delivered under circumstances of changing quarantine and lockdowns [20]. To this end, there is scope to test out the efficacy of this adapted version of PM + in LMICs, where the video teleconferencing modality may offer unique benefits for addressing instances of stigma and marginalisation in seeking mental health assistance.

Despite the success of scalable interventions, an outstanding question is clarification of the extent to which treatment gains are attributable to the strategies taught in the programs or to non-specific treatment effects such as counsellor attention or group involvement. All trials of PM + have compared the intervention with usual care, and in doing so have not disentangled these elements. To address this gap, the current study will assess the effectiveness of CWC delivered by lay peer facilitators to target distress resulting from the COVID-19 pandemic in a young adult population and compare this to non-directive group counselling. In using a non-specialist supportive framework involving peers to deliver this evidence-based program, we aim to address potential gaps in access to care, insofar as stigma may act as a barrier in young people utilising evidence-based care. A secondary aim of this study is to assess potential therapeutic impacts of attention and support afforded by peers in driving the effectiveness of CWC. We predict that CWC would lead to greater reductions in common mental health problems including worry, anxiety, depression, and suicidality relative to supportive counselling.

## Methods

### Aims & hypotheses

This study will assess the effectiveness of an adapted version of CWC to specifically target mental distress arising from the COVID pandemic in a cohort of university students in India. The randomized controlled trial (RCT) will compare CWC with Supportive Counselling (SC) in participants reporting moderate to severe psychological distress in a group format. The primary hypothesis is that those receiving group CWC will report lower psychological distress compared to those who received supportive counselling. To this end, we hypothesize that the impact of social support and alliance afforded by the supportive counselling condition will not exceed the therapeutic effects of evidence-based skills covered in CWC. The primary outcome measures are anxiety and depression, as measured by the Hospital Anxiety and Depression Scale (HADS, [21] subscales.

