### Primary outcome

The primary outcome will be severity of anxiety and depression symptoms as measured using the Hospital Anxiety and Depression Scales (HADS) [25]. The HADS is a 14-item scale consisting of two sub-scales: HADS-A (Anxiety, 7 items, range 0–21) and HADS-D (Depression, 7 items, range 0–21). Higher scores indicate more severe anxiety and/or depression. The minimal clinically important difference (as based on the effect size approach) has been determined at 1.32 for HADS-A and 1.40 for HADS-D and 1.17 for the HADS total score [26].

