### Statistical analysis

Baseline comparability between CWC and SC conditions will be analysed using multiple planned comparisons for continuous measures, and chi-squared tests for categorical variables. Hypothesis testing involving assessment of differential change over time between groups will be assessed using Hierarchical Linear Mixed Modelling (HLM). This HLM statistical method presumes an intent-to-treat framework by allowing the number of observations to vary between participants and thereby effectively handles missing data. For each outcome, linear effects of time of measurement, condition, and condition-by-time interaction will be analysed. Fixed effects parameters for the time of assessment and intervention condition will be tested with the Wald test (t-test, *p* < 0.05, two-sided) and 95% confidence intervals. Cohen’s (d) effect size will be calculated for all analyses. Analyses will focus on the primary outcome (HADS) and secondary outcomes (GAD-7, CSS, SIDAS, & WHO-5) for both CWC and SC, with the main outcome time point being the 2-month follow-up, relative to baseline. To assess for potential bias from attrition, completer analyses will also be conducted using only the data on participants completing the allocated intervention as planned. Two-tailed tests will be reported with a significance level of *p* < 0.05 for all analyses.

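### The two HADS subscales are named as primary measures, other sections speak of one primary outcome, and every test is set at 0.05 with no rule for what counts as success

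*Protocol article*

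**What the plan says.** All references are to the protocol article.

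- **Aims & hypotheses** gives one hypothesis: "The primary hypothesis is that those receiving group CWC will report lower psychological distress compared to those who received supportive counselling". It then names the measures in the plural: "The primary outcome measures are anxiety and depression, as measured by the Hospital Anxiety and Depression Scale". The same sentence ends by specifying the subscales.
- **Primary outcome** uses the singular, "The primary outcome will be severity of anxiety and depression symptoms as measured using the Hospital Anxiety and Depression Scales (HADS", and describes the instrument by its parts: "The HADS is a 14-item scale consisting of two sub-scales". It quotes minimal important differences for HADS-A (1.32), HADS-D (1.40) and the total (1.17), and does not say which score is primary.
- **Sample size** rests on one two-group comparison of the primary outcome at two months: effect size 0.6, two-sided alpha 0.05, power 0.95, 90 per arm, 200 enrolled after 10% attrition. It does not name the score.
- **Statistical analysis** again uses the singular: "Analyses will focus on the primary outcome (HADS) and secondary outcomes". It fixes the error rate for everything: "Two-tailed tests will be reported with a significance level of" p < 0.05, for all analyses.

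The instrument (HADS) and the primary time point (T2, two months) are fixed consistently in these sections. What remains open is which HADS score or scores decide the trial, and by what rule.

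**The concern.** Read literally, the Aims section and the blanket 0.05 level together give two primary tests, HADS-A and HADS-D at T2, each at the full 5%. The sections that speak of one primary outcome imply a single test. These are different trials in terms of error control.

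The difference shows if the result is split, with one subscale significant and the other not. Under the Aims wording that could be reported as a primary success. Under a both-required rule it would be a failure. Under a single-score reading it would depend on which score was meant. The trial's claim is superiority over an active comparator, so the rule that decides success should not be open to interpretation once results are known.

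**Working it through.** **1. The plan's own sample size figure.** Inputs from the Sample size section: d = 0.6, two-sided alpha 0.05, power 0.95.

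n per arm = 2(z₀.₉₇₅ + z₀.₉₅)² / d² = 2(1.960 + 1.645)² / 0.36 = 72.2, so 73 (74 by the t-test). The stated 90 per arm is not reproduced. It is larger than the inputs require: 90 per arm gives power 0.981, since 0.6 × √45 − 1.960 = 2.065. The attrition step is reproduced: 180 / 0.90 = 200. The mismatch is a separate matter and runs in the conservative direction, but it matters for step 4.

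**2. Error rate if either subscale suffices.** One T2 test per subscale, each at two-sided 0.05, no true effect on either. If the tests are independent: 1 − 0.95² = 0.0975. If they are correlated: 1 − P(|Z₁| < 1.96 and |Z₂| < 1.96), bivariate normal. The document gives no correlation between the subscales, so the values below are assumptions.

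| Assumed correlation | At least one false positive | At least one false positive favouring CWC |
|---|---|---|
| 0 | 0.0975 | 0.0494 |
| 0.3 | 0.0951 | 0.0476 |
| 0.5 | 0.0907 | 0.0454 |
| 0.7 | 0.0835 | 0.0417 |
| 0.9 | 0.0704 | 0.0352 |

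The nominal values are 0.05 and 0.025. At correlations of 0.7 to 0.3 the two-sided rate is 1.7 to 1.9 times nominal (0.0835 / 0.05 and 0.0951 / 0.05).

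**3. Error rate under the other rules.** If both subscales must be significant at 0.05, a false claim requires a false positive on at least one subscale that has no effect, so the rate cannot exceed 0.05. If one score is primary, there is one test at 0.05.

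**4. Power under each rule,** at d = 0.6 on each subscale and before any allowance for clustering by treatment group.

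- *Bonferroni, 0.025 each.* Error rate 0.0494 if independent, 0.0465 at correlation 0.5. Required n = 2(2.241 + 1.645)² / 0.36 = 83.9, so 84 (t-test 85.2, so 86). Power per subscale at 90 per arm: 0.6 × √45 − 2.241 = 1.784, giving 0.963 (0.960 by the t-test). Holm is never less powerful than Bonferroni.
- *Both required at 0.05.* Power at 90 per arm is 0.961, 0.964 and 0.967 at correlations 0, 0.5 and 0.7.
- *One score at 0.05.* Power 0.981.
- *If 90 are randomised per arm, as in the Abstract, and 10% are lost,* 81 per arm are analysed. Power at alpha 0.025 is then 0.943, against 0.968 at 0.05.

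**The case against.** The strongest reply is that no section states an either-subscale rule. A both-required rule or a single primary score fits the wording too, and neither inflates the error rate. This stands, and it is why the 8.4% to 9.5% must be given as conditional. A reader might infer that the trial simply runs at nearly double its stated error rate. The document does not support that: the figure needs the either-subscale rule, and its upper end needs subscales that are close to independent.

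A second reply is that success rules and multiplicity procedures are commonly left to the statistical analysis plan, and that a journal article condenses. This stands only in part. The article does not merely omit the rule. It describes the primary outcome in two different ways and fixes 0.05 for every analysis.

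Third, HADS in the Statistical analysis section may be shorthand for the instrument, so that the singular wording is loose and not a rival definition. That is possible. It would leave two primary measures, each at 0.05, which is the case where a rule is most needed.

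Two further readings are tempting and should be set aside:

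- A reader might infer that psychological distress is a rival primary outcome, measured only by the K-10 at baseline. The Abstract says "The primary outcome will be reduction in psychological distress including anxiety and depression at 2-months post treatment", and Aims & hypotheses gives the HADS as the measure in the same paragraph as the hypothesis. Distress is the construct, and the K-10 is the screener.
- A reader might count the HADS total as a third primary test. The total appears only among the minimal important differences, and no section plans a test of it.

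**Conclusion.** The inconsistency is real and lies in the protocol text: two primary subscales in one section, one primary outcome in three others, a 0.05 level for all analyses, and no rule linking them. The consequence is conditional. If either subscale suffices, the chance of a false-positive primary result is about 8.4% to 9.5% at assumed correlations of 0.7 to 0.3, with 9.75% under independence. If both are required, or one score is primary, it is at most 5%.

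A reader might also infer that the sample size is inadequate for two primaries. On the stated inputs it is not: 84 to 86 per arm suffice at alpha 0.025, and 90 are planned. This assumes that the 90 are analysed, as enrolment of 200 with 10% attrition implies. It also assumes an effect of 0.6 on each subscale and makes no allowance for clustering.

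**What to change.** Align Aims & hypotheses, Primary outcome, Sample size and Statistical analysis on one rule, settled before outcome data are examined by arm:

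- **(a)** keep HADS-A and HADS-D as co-primaries, with Holm or Bonferroni control across the two T2 tests;
- **(b)** require both subscales to be significant at two-sided 0.05; or
- **(c)** name one HADS score at T2 as the single primary and make the other scores secondary.

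Replace the blanket 0.05 statement with the chosen rule for the primary analysis, and restate the power to match.

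The cost is wording and a small loss of power. At 90 analysed per arm, power goes from 0.981 for a single test to about 0.96 per subscale under (a), or about 0.96 for joint success under (b). Option (c) costs no power for the chosen score, assuming the effect on it is also 0.6. No extra recruitment is needed on the protocol's own inputs, provided that 200 are enrolled as the Sample size section states.

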### Design & setting

This study is designed as a single-blind, parallel RCT that will be conducted in a university setting in Bangalore, India. The study design will employ a 2 (Treatment Condition) x 4 (Assessment Point) factorial design (see Fig. 1). Participants will be assessed at baseline (T0), post-intervention (T1), and two-( T2) and six-month (T3) follow-ups. The primary outcome time point is set at (T2). This trial was registered on Australian New Zealand Clinical Trials Registry (ACTRN12621001064897) on August 12, 2021 and received ethical approval from CHRIST University in Bangalore, India (ID: CU: RCEC/64/10/21).

**Fig. 1 Fig1:**
[figure not shown]
Flow diagram of study

Both interventions will be delivered via the Google Meet videoconferencing platform via the CHRIST (Deemed to be University) network that is compliant with the Health Insurance Portability and Accountability Act (HIPPAA). This online platform was chosen as both facilitators and students were familiar with this platform as it was been used for online university classes.

### Participants

Participant inclusion criteria are (a) college-attending young adults (18–25 years); (b) score above 20 on a screening questionnaire for psychological distress (Kessler-10; K-10); and (c) report sufficient English language comprehension. Exclusion criteria are: (a) current psychosis; (b) imminent suicidal risk; (c) current substance dependence (but not abuse); or (d) report of not having access to internet-based teleconferencing facility.

### Recruitment and informed consent

Participants will be identified through university-wide screening via physical advertisements where informed consent will be obtained using a two-step procedure: [1] to conduct screening and [2] to take part in the RCT. Individuals who express interest in taking part in the study will read an explanation of the trial, and then provide informed consent at step one. Those meeting inclusion criteria will proceed to the second step. Those who screen positive will then be sent the T0 assessments.

### Assessment or eligibility and screening

Following receipt of consent, participants will be directed to a webpage that will include the Kessler-10 (K-10); if participants score ≥ 20 on the K-10 they will be directed to complete the T0 assessments. If participants are not selected because they score below the cut-offs for the K-10, they will be provided feedback on their test outcomes and reasons why they are not eligible for the study will be explained to them. If participants meet any of the exclusion criteria, as relevant, participants will be provided with crisis support services, and be provided with external referrals for further management with specialised services including the option to seek support via the internal CHRIST university counselling support service. Pre-assessment (T0) consists of the following instruments to measure primary and secondary outcomes: Hospital Anxiety and Depression Scales (HADS), Generalized Anxiety Disorder Scale (GAD-7), World Health Organization Well-Being Index (WHO-5), Coronavirus Stress Scale (CSS), and Suicidal Ideation Attributes Scale (SIDAS).

### Randomization

The randomization will be conducted by a computerized software on a 1:1 basis and will occur following completion of the T0 assessment. Two project managers who are independent of any other aspects of the treatment study being conducted in Bangalore, India will allocate individuals to CWC or SC groups. Following this time, individuals will be invited for the introductory online session with the group facilitator.

### Introductory online session

After informed consent, and prior to the commencement of groups, participants will be contacted to partake in an initial 15–20-minute introductory online session with a peer facilitator. The aims of this session will be to establish initial rapport between the participant and their facilitator. During this session, participants will also be given basic information relating to how the group sessions will run as well as an explanation of how to use the online teleconferencing platform (Google Meet).

### Interventions

*Coping with COVID* (CWC). The CWC programme is a brief psychological intervention developed to reduce symptoms of stress (e.g., depression, anxiety) for those affected by ongoing adversity. This programme was adapted to include evidence-based strategies that specifically target COVID-19 related distress in a young adult population. This includes education about common reactions to COVID-19, stress management (i.e., slow diaphragmatic breathing), problem solving, worry management, behavioural activation, skills to strengthen access to social support, and relapse prevention. CWC will be delivered over 6 weekly sessions of 60-minute duration. The programme will be delivered in anticipated group size of 4–5 participants via the Google Meet online platform.

*Supportive Counselling (SC).* The SC arm will involve 6 weekly 60-minute video-conferencing sessions that will be led by a trained peer facilitator, who will facilitate group discussions about how students are coping with the pandemic, ventilation of reactions to problems experienced, and discussion of possible solutions. Those randomised to the SC arm will not receive support relating to CWC strategies.

